#### Intervention strategy and regime

After the larvicide application optimization and study cluster randomization, we will treat each treatment cluster with LLML at the time interval of 4 or 5 months (Fig. 3). The first treatment will be conducted in February-March about 1 month before the beginning of the long rainy season which usually starts in April. After three treatments, we will perform no treatments for the next 8 months. This will provide useful data on the dynamics of action of the LLML and the waning efficacy of LLML over time. These data will be important in analyzing cost-effectiveness to help optimize the timing of re-treatments. After 8 months, a total washout of the LLMLs will be assumed to have taken place. Next, we will perform a crossover and switch of the control and treatment clusters. Former control clusters will receive three rounds of LLML treatment at appropriate time intervals, and the former treatment clusters will receive no LLMLs. This strategy will minimize ascertainment biases that might be attributed to care-seeking behaviors of the population or to malaria detection and reporting by malaria treatment clinics. We will test LLMLs manufactured by Central Life Sciences. The larvicide application regime is as follows: temporary, semipermanent, and permanent habitats will be treated with FourStar controlled release granule formulation, 90-day briquettes, and 180-day briquettes, respectively. Application dosage will follow the recommendation of the manufacturer: 10 lbs per acre of water surface for the granule formulation, and 100 ft^2^ water surface per briquette.

We will conduct monthly vector surveys throughout the study period (Fig. 3) to determine indoor- and outdoor-biting vector abundance, using the same sample size of 64 trap-nights per cluster per month, and sporozoite infection and mosquito blood meal analysis will be conducted on all collected specimens. To confirm larviciding efficacy, we will examine larval abundance, age structure, and pupal productivity on a monthly basis in 100 randomly selected larval habitats each from treatment and control sites using our GIS maps and data on sites where LLML was applied.

#### Sample size justification

Sample size was calculated based on 2010 and 2011 active case surveillance results from Iguhu and Emutete areas [47]. Then the number of clusters required and the number of individuals required for each cluster were calculated following the methods developed by Hayes and Bennett based on cluster-randomized trials assuming equal population for each cluster [59]. The observed malaria incidence rate was 52.7 cases per 1000 people year in 2011. We calculated the numbers of clusters (matched-pairs) and individuals required for epidemiological (clinical malaria) assessment of the long-lasting larvicide treatments to detect a 50 % protective efficacy conferred by the treatment compared with the reference group (no treatment), with a power of 80 %, significance level of 5 % and the coefficient of variation of true proportions between clusters within each treatment was assumed to be 0.15. The estimated number of clusters (matched-pairs) for the intervention will be five and the required number of individuals for each matched-pair will be 1196; assuming a design effect of 0.25 and 20 % of subjects lost to follow-up. The estimated number of clusters (matched-pairs) for the intervention will be seven and the required number of individuals for each of the matched-pairs will be fewer than 2000. The 28 clusters proposed in the randomized cluster study will detect 50 % malaria incidence reduction with 99.9 % power and 30 % incidence reduction with 85.3 % power. This is based on the current malaria incidence rate in the study sites (52 clinic cases per 1000 population year) and a two-tailed alpha with a human population size of 2000 per cluster (Table 1). If the malaria incidence is 50 % lower than the current value, the design will still detect 50 % incidence reduction with 99.7 % power and 40 % reduction with 95.2 % power (Table 1).

**Table 1 Tab1:** Calculated power (%) to detect various levels of incidence reduction under three incidence scenarios

Annual incidence rate (cases/1000 population)	Malaria incidence reduction			
	50 %	40 %	30 %	20 %
Observed in the site: 52	99.9	98.7	85.3	48.6
Low-incidence value: 26	99.7	95.2	74.4	38.9
High-incidence value: 78	99.9	99.3	89.0	53.0

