**Fig. 1 Fig1:**
[figure not shown]
Map of study area and distribution of clinics and hospitals with catchment areas overlapping the study area

Local residents are predominantly farmers and depend upon farming, cattle and goat herding for subsistence. Malaria transmission is seasonal, with two peaks in vector abundance reflecting the bimodal rainfall pattern: a major peak between April and June and a minor peak between October and November [43]. Most malaria is caused by *Plasmodium falciparum* [12]. The main malaria vectors in the area are *An. gambiae* s.s., *An. arabiensis*, and *An. funestus* s.l. [43, 44]. Malaria vector density was high in the early 2000s, decreased substantially during 2006–2008 after the first round of mass distribution of ITNs in 2006, and has gradually increased since 2008 [12]. Pyrethrum spray collections (PSC) of indoor-resting *Anopheles* were about 1.0 females/house/night in 2014 compared to 0.1 females/house/night in 2007 [12, 45]. Cross-sectional community-level surveys in May 2011 indicated that parasite prevalence averaged 11.8 % in the general population (all ages) but varied between localities from 3.3 % to 25.4 % [44]. In school children aged 6–13 years, surveys in 2012 found an average parasite prevalence of 27.2 %, which varied from 18.8 to 35.4 % among villages [45, 46]. Active case surveillance through bi-weekly home visits in May 2011 indicated an average annual clinical malaria incidence rate of 31.4 cases per 1000 people in the general population, varying from 28.9 to 36.2 between villages [47]. Ownership of ITNs (mainly long-lasting insecticidal nets) ranged from 78.3 to 84.2 % in 2013 [48]. There have been several attempts in the past 10 years to control malaria vectors in the study area using conventional formulations of *Bti*/*Bs* (i.e., through weekly re-treatment of larval habitats) and IRS [35, 39, 44, 49]. The last community-wide mass distribution of ITNs was undertaken by the Division of Malaria Control (DOMC) of Kenya in 2014. Currently there is no mass distribution of ITNs or IRS and no larviciding in the proposed study area.

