There are also limitations for the design. The incidence of clinical malaria is essential for the evaluation of intervention success. However, as pointed out by previous studies [47, 72], crude health facility records are not always a reliable source of such information and may in fact under estimate the true clinical incidence rate [47, 72]. However, as long as clinical malaria was diagnosed the same way across all health care facilities, comparison between intervention and control groups is justified. EIR is a good measure of reduction in transmission since larval control reduces overall vector population density and EIR is measured based on vector population density. Additional indicators, such as clinical incidence through active case surveillance, can be a more accurate estimate of incidence, and parasite prevalence through cross-sectional surveillance may be helpful. However, as per restrictions imposed by the funding policy, direct measures of human subjects are restricted.

Despite very high bed net coverage, malaria incidence in many African sites is resurging after a short-time reduction when ITN and IRS scale-up was initially rolled out. This malaria resurgence is caused primarily by increases in insecticide resistance and outdoor transmission. New cost-effective methods beyond bed nets and IRS are urgently needed. Long-lasting microbial larviciding represents a promising new tool that can target both indoor and outdoor transmission and alleviate the problem of pyrethroid resistance. Comprehensive evaluation of potentially cost-effective LLML will provide critically needed data for determining whether LLML can be used as a supplemental malaria control tool to further reduce malaria incidence in Africa.

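### The power table rests on one unsourced between-cluster CV of 0.15 that is never varied, and its cells match 7 pairs, not the trial's 14; for 28 clusters the printed power for 20 to 40 % reductions depends on the CV.

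*Protocol article*

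**What the plan says.** The Sample size justification in the protocol article plans the trial "following the methods developed by Hayes and Bennett based on cluster-randomized trials assuming equal population for each cluster". The test is two-sided at 5 %, the target is a 50 % reduction, and the requirement is 80 % power. On variation it says that "the coefficient of variation of true proportions between clusters within each treatment was assumed to be 0.15", without a reference or derivation. It first arrives at five matched pairs, then at seven. It goes on to credit the 28 clusters with 99.9 % power for a 50 % reduction and 85.3 % for a 30 % reduction, at 52 cases per 1000 and 2000 people per cluster.

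Table 1 is captioned "Calculated power (%) to detect various levels of incidence reduction under three incidence scenarios". Its dimensions are annual incidence (26, 52, 78 per 1000) and reduction (20 to 50 %). The CV does not appear in it.

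The Randomization section sorts the 14 clusters of each county into seven blocks of two by rank score. Two counties therefore give 7 × 2 = 14 pairs.

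The Study area section reports three measures of local spread:
- Clinical incidence from home visits: mean 31.4 per 1000, range 28.9 to 36.2 between villages.
- Schoolchild prevalence: mean 27.2 %, range 18.8 to 35.4 %.
- All-age parasite prevalence: mean 11.8 %; it "varied between localities from 3.3 % to 25.4" %.

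The primary endpoint comes from government facility records only. The Discussion concedes that "crude health facility records are not always a reliable source of such information".

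**The concern.** In a cluster trial with about 2000 people per cluster, most of the variance of the comparison comes from differences between clusters. The CV then deserves a source and a sensitivity range more than any other input. Here it has neither, and one of the protocol's own series shows much wider spread than 0.15. That series is not the endpoint. The series closest to the endpoint was collected by home visits, which do not carry differences in care-seeking and reporting between clusters.

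The number of pairs behind Table 1 is a second problem. If the table was not computed for the 28 clusters it is said to describe, its figures are the power of this trial neither at 0.15 nor at any other stated CV.

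At stake is how a non-significant result is read. A reader who takes 85.3 % for a 30 % reduction, or 98.7 % for 40 %, as a property of the design would treat a null result as fairly strong evidence against an effect of that size. If the CV is well above 0.26, that reading would be too strong.

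**Working it through.** **Formula.** The matched-pair rate formula of the cited method, solved for power:

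Power = Φ( √[ (c − 2)(λ0 − λ1)² / { (λ0 + λ1)/y + k²(λ0² + λ1²) } ] − 1.96 )

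Here c is the number of pairs, λ0 and λ1 the control and treated rates, y the person-years per cluster and k the CV. From the sample size section: λ0 = 0.052, y = 2000, k = 0.15, two-sided 5 %.

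**Step 1: reproduce the 30 % cell.** λ1 = 0.7 × 0.052 = 0.0364.
- (λ0 − λ1)² = 0.00024336
- (λ0 + λ1)/y = 0.0884/2000 = 0.0000442
- k²(λ0² + λ1²) = 0.0225 × 0.00402896 = 0.0000907
- Denominator = 0.0001349; the CV term is about two thirds of it.

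With c = 7: √(5 × 0.00024336/0.0001349) = 3.004; minus 1.96 = 1.044; power 85.2 % (printed 85.3 %).

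With c = 14: √(12 × 0.00024336/0.0001349) = 4.654; minus 1.96 = 2.694; power 99.6 %.

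**Step 2: all cells at 7 pairs and k = 0.15** (computed / printed, %).

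| Incidence per 1000 | 50 % | 40 % | 30 % | 20 % |
|---|---|---|---|---|
| 52 | 100.0 / 99.9 | 98.6 / 98.7 | 85.2 / 85.3 | 48.4 / 48.6 |
| 26 | 99.7 / 99.7 | 95.1 / 95.2 | 74.1 / 74.4 | 38.7 / 38.9 |
| 78 | 100.0 / 99.9 | 99.3 / 99.3 | 88.9 / 89.0 | 52.9 / 53.0 |

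Every cell agrees within 0.3 points. The table was not built from 14 pairs with a larger CV: at c = 14 and k = 0.26 the 30 % column would be 85.9, 81.2 and 87.5 % for 52, 26 and 78 per 1000, against the printed 85.3, 74.4 and 89.0 %.

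**Step 3: 14 pairs, 52 per 1000, CV varied** (power, %).

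| CV | 50 % | 40 % | 30 % | 20 % |
|---|---|---|---|---|
| 0.15 | 100.0 | 100.0 | 99.6 | 84.5 |
| 0.25 | 100.0 | 99.2 | 88.1 | 51.7 |
| 0.30 | 99.8 | 96.2 | 76.4 | 40.0 |
| 0.35 | 98.8 | 90.1 | 64.4 | 31.7 |
| 0.45 | 91.8 | 72.9 | 45.3 | 21.5 |

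At 52 per 1000, the 30 % cell equals the printed 85.3 % at k ≈ 0.263 and falls to 80 % at k ≈ 0.285. A 50 % reduction falls to 80 % at k ≈ 0.54.

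**Step 4: which input moves power.** For a 30 % reduction, halving incidence changes power from 99.6 to 98.1 % with 14 pairs, and from 85.2 to 74.1 % with 7. Doubling the CV from 0.15 to 0.30 changes it from 99.6 to 76.4 % with 14 pairs, and from 85.2 to 40.9 % with 7. The CV matters more on either basis.

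**Step 5: what the protocol's own ranges imply.** The numbers of localities and villages are not given, so these are assumptions.
- Village incidence: range/4 gives (36.2 − 28.9)/4/31.4 = 0.06. Two villages at the extremes would give 0.16. This is compatible with 0.15 or less.
- School prevalence: range/4 gives (35.4 − 18.8)/4/27.2 = 0.15. Dividing by the expected normal range for 10 or 5 villages gives 0.20 or 0.26.
- All-age prevalence: the smallest possible observed CV puts one locality at 3.3, one at 25.4 and the rest equal, so that the mean is 11.8. This gives 0.26 for 28 localities, 0.31 for 20, 0.46 for 10, and 0.19 for 50.

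**The case against.** A reader might infer that the protocol's local data place the CV at 0.26 or higher, and that the stated power is therefore unsupported. The documents do not carry that.

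- Only one of the three series is clearly above 0.15. All-age prevalence is not the endpoint, its observed spread includes sampling error, and the bound of 0.26 requires 28 localities or fewer. The only series on clinical incidence points to about 0.15 or less.
- At a CV of 0.26 the 28 clusters still give 85.9 % for a 30 % reduction and about 100 % for 50 %. Because Table 1 was computed with 7 pairs, its figures leave room up to about 0.26.
- The 50 % reduction at 80 % power, which is the design target, survives every CV in the table above.
- The matched-pair formula needs the within-pair CV. Pairing within county on a score that gives incidence a weight of 5 out of 9.5 should make this smaller than the crude spread between localities.
- The crossover observes each cluster under both conditions, so stable differences in facility capture should largely cancel. The protocol gives no figure for capture, and a value such as 30 to 70 % would be pure assumption.

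All of this stands, and it limits the point. It does not remove it. The protocol offers no within-pair CV and credits no gain from crossover in Table 1. Nor does it present the room up to 0.26 as intended: it arises only because the pair count and the cluster count do not match. Confidence intervals at the end will help a reader of a null result, but they do not correct a power statement made in advance.

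**Conclusion.** The point holds in a limited form. The CV of 0.15 is unsourced, it is the most influential input, and it is the one that Table 1 does not vary. The table's figures are those of 7 pairs, while the text attributes them to 28 clusters. For 14 pairs at 52 per 1000, power for a 30 % reduction is 99.6 % if the CV is 0.15, matches the printed 85.3 % at about 0.263, and drops to 76.4, 64.4 and 45.3 % at 0.30, 0.35 and 0.45. The consequence is confined to reductions of about 20 to 40 %.

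The documents do not show that the trial is underpowered. They show that its power for moderate reductions is undetermined until the CV of facility-recorded incidence is known. Facility records may widen the spread by an amount the documents do not quantify; pairing and crossover will offset part of it. The calculation assumes the cited formula, equal clusters of 2000 person-years and no credit for crossover.

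**What to change.** 1. Recompute Table 1 for 14 pairs, with the CV as a dimension (for example 0.15, 0.25, 0.35, 0.45), and state the number of pairs in the table.
2. Make the power claims for 20 to 40 % reductions conditional on the CV. The claim for the 50 % target can stay, with the note that power is at least 80 % up to a CV of about 0.54 at 52 per 1000.
3. Before the first treatment, estimate the between-cluster and within-pair CV of facility-recorded incidence from the baseline data already collected for the 28 clusters. Subtract the Poisson variance first: at 52 per 1000 and 2000 person-years a cluster has 104 expected cases, so chance alone gives a CV of 1/√104 = 0.098. The pairs are formed partly on the same baseline incidence, so the within-pair value will tend to look too small; report both values.
4. Report the detectable reduction at the estimated CV.

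The cost is one recalculated table and a short calculation on existing data. The stated power may become less favourable. No clusters, staff or data are added.

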Using these data, each cluster will be allocated to either treatment or control through randomization using the following procedures. First, each of the four parameters listed above will be standardized with the highest cluster as 1. Second, we will assign the highest weight for clinical malaria cases (weight = 5), the lowest weight for human population size (0.5), and intermediate weights for expected vector density (2) and larval habitats (2), following the method of Corbel et al*.* [58]. For each cluster a rank score will be computed as the sum of weighted clinical malaria incidence, vector density, habitat abundance, and human population size. Finally, the 14 clusters within each county will be sequentially numbered according to their rank scores and sorted into seven blocks of two clusters having successive rank scores. We expect the two clusters within each block to have similar risk characteristics for clinical malaria, vector abundance, larval habitats, and human population size. In each block, the ranks of the two clusters are put into two sealed envelopes, one cluster will be randomly allocated to treatment and another to control, using computer-generated random numbers (0 – control, 1 – intervention).

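### The power credited to 28 clusters, including all of Table 1, is reproduced by 7 matched pairs (14 clusters), not by the 14 pairs the trial randomises

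*Protocol article*

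**What the plan says.** All references are to the protocol article.

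- **Method** (Sample size justification): clusters and individuals were "calculated following the methods developed by Hayes and Bennett based on cluster-randomized trials assuming equal population for each cluster", for matched pairs.
- **Inputs** (same section): an observed incidence of 52.7 per 1000 per year, later rounded to 52; "the coefficient of variation of true proportions between clusters within each treatment was assumed to be 0.15"; "with a power of 80 %, significance level of 5" %; and, for the power figures, "a two-tailed alpha with a human population size of 2000 per cluster".
- **Requirement** (same section): first five pairs with 1196 individuals, "assuming a design effect of 0.25 and 20 % of subjects lost to follow-up"; then "The estimated number of clusters (matched-pairs) for the intervention will be seven", with fewer than 2000 individuals.
- **Power claim** (same section): "The 28 clusters proposed in the randomized cluster study will detect 50 % malaria incidence reduction with 99.9 % power", and 85.3 % for a 30 % reduction. Table 1 gives 12 power values, for three incidence rates and four reductions.
- **Allocation** (Randomization): "the 14 clusters within each county will be sequentially numbered according to their rank scores and sorted into seven blocks of two clusters". With two counties this is 14 pairs, or 28 clusters.

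**The concern.** The power statement names 28 clusters, but the last requirement before it is seven pairs, and seven is also the number of pairs in one county. If the table was computed for seven pairs, the label does not match the calculation.

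This is the article's only power statement for the primary endpoint, and readers will judge a null result and the smallest detectable effect against it. As printed, a 20 % reduction at the observed incidence has about even odds of detection (48.6 %). A reader would then excuse a null result as uninformative about effects of that size, which may be wrong for the design that is actually randomised.

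**Working it through.** **Formula.** The Hayes-Bennett matched-pair formula for rates, solved for power:

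power = Φ( (λ0 − λ1) / √{ V / (c − 2) } − 1.96 ), with V = (λ0 + λ1)/y + k²(λ0² + λ1²)

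**Inputs.** From the Sample size justification: k = 0.15, y = 2000, two-sided 5 % (1.96), λ0 = 0.0527. Here y is in person-years, so one year of follow-up is assumed; the rates are annual. The low and high rates are half and one and a half times λ0 (0.02635 and 0.07905), printed as 26 and 78 per 1000. c is the number of pairs.

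**Step 1: one cell by hand, 30 % reduction at 52.7 per 1000.**

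- λ1 = 0.7 × 0.0527 = 0.03689; λ0 − λ1 = 0.01581
- V = 0.08959/2000 + 0.0225 × (0.002777 + 0.001361) = 0.00004479 + 0.00009311 = 0.0001379; √V = 0.011743
- c = 7: 0.01581 × √5 / 0.011743 = 3.010; Φ(3.010 − 1.96) = 85.3 %, as printed
- c = 14: 0.01581 × √12 / 0.011743 = 4.664; Φ(4.664 − 1.96) = 99.7 %

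**Step 2: the whole of Table 1 (power, %).**

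| Rate per 1000 | Source | 50 % | 40 % | 30 % | 20 % |
|---|---|---|---|---|---|
| 52 | Printed | 99.9 | 98.7 | 85.3 | 48.6 |
| 52.7 | 7 pairs | 99.97 | 98.68 | 85.32 | 48.60 |
| 52.7 | 14 pairs | >99.9 | >99.9 | 99.66 | 84.66 |
| 26 | Printed | 99.7 | 95.2 | 74.4 | 38.9 |
| 26.35 | 7 pairs | 99.69 | 95.18 | 74.39 | 38.89 |
| 26.35 | 14 pairs | >99.9 | >99.9 | 98.18 | 73.86 |
| 78 | Printed | 99.9 | 99.3 | 89.0 | 53.0 |
| 79.05 | 7 pairs | 99.99 | 99.33 | 89.03 | 53.00 |
| 79.05 | 14 pairs | >99.9 | >99.9 | 99.86 | 88.36 |

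With seven pairs, ten cells agree to the printed decimal. The other two (99.97 and 99.99) agree if 99.9 was printed as a cap. With the rounded rates 52, 26 and 78 instead, every cell is within 0.3 points. With 14 pairs the largest gap is 36 points (20 % reduction at 52 per 1000).

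**Step 3: could 28 clusters give Table 1 some other way?** With 14 pairs and y = 2000, the search covered k from 0.05 to 0.44, small-sample terms of 0, 1 or 2, and normal or t-based power. The best fit still misses a cell by 4.7 points. Reading the 0.25 as k, with t-based power, comes close in the 52 row (85.6 and 48.7 for 30 % and 20 %) but fails the 26 row (80.5 against 74.4; 43.7 against 38.9). Fourteen pairs fit within 1 point only with y about 800 to 1000 and k about 0.23, neither of which the article states.

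**Step 4: the 0.25.** Applied literally as a multiplier, with 20 % loss, it gives 1196 × 0.25 / 0.8 = 374, which shrinks the sample while the text moves up to seven pairs. A 25 % inflation gives 1196 × 1.25 / 0.8 = 1869, which fits the bound of 2000. So does no design effect at all: 1196 / 0.8 = 1495, and 5 / 0.8 = 6.25, which rounds up to seven pairs.

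**The case against.** The strongest defence is that the provenance of Table 1 is inferred. The article never gives its pair count. Strictly, only c − 2 = 5 is identified, and 14 pairs with k = 0.232 and y = 833 give practically the same numbers. This stands as a limit on wording: the table is reproduced by seven pairs, not proven to have been computed for them. It does not rescue the label, because the stated k and y fit seven pairs in every cell and no 14-pair variant tried with y = 2000 does. That the table shows the power of one county is a plausible guess and no more.

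The second defence is that the discrepancy is conservative and the planned 50 % effect has at least 99.7 % power either way. That is correct. No cluster count, allocation or analysis changes.

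A reader might draw several stronger conclusions that the article does not support:

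- *The trial is underpowered.* At the stated inputs, 28 clusters have more power than printed.
- *The 28 clusters are adequately powered for a 20 % reduction.* This holds at 52 and 78 per 1000 with k = 0.15, not at 26 per 1000 (about 74 %). At the 31.4 per 1000 in the Study area section, 14 pairs give 77.2 %. If 0.25 were the coefficient of variation, 14 pairs would give about 52 % at 52 per 1000.
- *The design effect must be 1.25.* Step 4 shows that other readings fit too.
- *Five and seven pairs are rival requirements.* They can be read as before and after inflation for design effect and loss.
- *Leaving out the crossover is an error.* Power for one parallel comparison is a legitimate basis, and a condensed article may leave the rest to the full protocol.

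**Conclusion.** The point holds as a mislabelled power calculation. For the 28 clusters named, and on the article's own inputs, power for 30 % and 20 % reductions is about 99.7 % and 85 % at 52 per 1000 (printed 85.3 and 48.6), 98 % and 74 % at 26 per 1000 (printed 74.4 and 38.9), and 99.9 % and 88 % at 78 per 1000 (printed 89.0 and 53.0). The printed figures understate the power of the design.

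This rests on k = 0.15, 2000 person-years per cluster, the normal approximation with the c − 2 term, and no gain from the baseline or crossover periods. Across the normal and t-based variants, 14 pairs at 52 per 1000 give 99.0 to 99.9 % for a 30 % reduction and 78.5 to 89.5 % for 20 %. With 1600 person-years (20 % loss) they give 99.4 % and 81.7 %. None of these approaches the printed 85.3 and 48.6.

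**What to change.** 1. Recompute Table 1 and the power figures in the text for 14 matched pairs, or relabel them as the power of seven pairs.
2. State beside the table the number of pairs, the coefficient of variation and the person-years per cluster used.
3. Explain the 0.25. Taken literally as a design effect it is below 1 and would reduce the sample. A 25 % inflation (1.25) is one reading that fits, for the sponsor to confirm.
4. Say that the five-pair and seven-pair figures are before and after inflation, if that is what is meant.

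The cost is one recomputed or relabelled table and a few sentences. Nothing in the conduct of the trial changes.
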